# Interaction-focused music therapy with cancer-affected children and their significant others: a randomized controlled feasibility study with subsequent intervention (INMUT)

**DOI:** 10.1186/s40814-024-01490-8

**Published:** 2024-05-28

**Keywords:** Music therapy, Paediatric oncology, Assessment of parent–child interaction (APCI), Feasibility randomized controlled trial, Family, Significant other, Systemic functioning, Psychological functioning, Psychosocial burden

## Abstract

**Background:**

Paediatric oncology/haematology patients and their families are confronted with a life-threatening situation for which music therapy can be a cross-linguistic field of action. The creative act of making music together offers the possibility to strengthen competences and make conflicts tangible. Besides its complementing of evidence-based biomedical care, there is little research on the feasibility and efficacy of interactive music therapy including the diagnosed child and their significant others.

**Methods:**

We conducted an assessor blind, prospective, multicentric feasibility randomized controlled trial (RCT) with subsequent intervention. Including overall 52 child-significant other dyads, INMUT investigates interaction-focused music therapy with cancer-affected children and their significant others (INMUT-KB; *n* = 21) compared to music therapy only with the child (MUT-K; *n* = 21) and a wait-list group (WLG; *n* = 10). The measurement points include the screening for a cancer diagnosis, psychometric baseline (pre-T1), initial assessment (T1/T2), music therapy sessions (T3–T9), final assessment (T10), final psychometric evaluation (post-T10), and 3-month follow-up (cat-T11). *Feasibility and acceptability* of the (1) research methodology, (2) intervention and (3) estimation of effect sizes will be assessed using qualitative and quantitative data. The *proposed primary outcome* includes the parent–child interaction (APCI), and the *proposed secondary outcomes* refer to subjective goal achievement (GAS), quality of life (KINDL), system-related functional level (EXIS), psychosocial stress (BAS), psychosomatic complaints (SCL-9k), and resources (WIRF). We plan to investigate the efficacy of INMUT-KB and MUT-K post-intervention (post-T10) within the RCT design and at 3-month follow-up (cat-T11).

**Discussion:**

This study will provide insights into the feasibility of INMUT and the final sample needed for a confirmatory RCT. We will reflect on successfully implemented study procedures and, if necessary, provide recommendations for changes considering the design, procedures, measures, and statistical analyses. The discussion will conclude with an evaluation whether a confirmatory RCT is worth the investment of future resources, including the calculated number of child-significant other dyads needed based on the efficacy trends derived from this feasibility study.

**Trial registration:**

ClinicalTrials.gov: NCT05534282; date of registration: June 23, 2022.

## Background

Music therapy has asserted itself as an interdisciplinary field of psychosocial care in paediatric oncology [1]. Since 2004, it is part of the professional profile of the Psychosocial Working Group for Paediatric Oncology and Haematology (PSAPOH) [2] and was anchored in the S3 guidelines of the PSAPOH in 2008 [3]. The inclusion of significant others in therapy is explicitly recommended in these guidelines. “Significant others” is a psychological term which has been adopted [4–7] to describe people who are close to the cancer-affected child, bearing responsibility and providing support, such as parents, grandparents, foster parents, godparents, and siblings. The practical implementation of the inclusion recommendation however is not satisfactory. Only about half of the German-speaking clinics provide music therapy [8]. Up to now, the legal health care system in Germany covers inpatient music therapy for single patients in an individual setting. Outpatient music therapy is not reimbursed by the health insurance companies. Although significant others often also appear to be clinically affected [9], they are neglected. Consequently, there is a large gap in the psychosocial support of children with cancer and their social environment [10].

### State of research

We conducted a systematic literature search on PubMed and Cochrane databases in German and English with the time restriction 2011 to 2023. In the PubMed database, 52 literature references were found, 30 sources were not included due to irrelevance, and 22 articles were preselected because they matched at least 3 of 4 search categories. Of those, 15 articles were examined in more detail because they matched all search parameters. The sample included two scoping reviews, seven exploratory practice reviews, five quantitative studies such as randomized controlled trials (RCTs) and a single case design pilot study, and one qualitative study (Table 1).*Scoping reviews*: The results showed that music therapy can address the needs of paediatric oncology patients and families and optimize their care [11]. Music therapy is suitable for promoting self-esteem; improving physical, emotional, and cognitive aspects related to the disease; and, to a lesser extent, alleviating physiological symptoms. Music therapy interventions are generally well received, not only by children and adolescents with cancer but also by their families and health professionals. Nevertheless, several gaps were identified in the studies reviewed, including a lack of specificity in terms of the outcomes achieved or the music therapy intervention methods used [12].*Exploratory practice reviews*: The importance of music in the lives of children and their parents in paediatric oncology is intensely discussed [13]. Music provides an experience of competence and interactive affect regulation [14] and thus is suggested to be a measure of quality improvement for the future growth of the music therapy profession [15]. A multicentric survey study highlights the importance of communication and collaboration between music therapists and the multidisciplinary care team using a model of family-centred care that actively involves parents and caregivers in music interventions, treatment planning, and care delivery [16]. In a feasibility and acceptability report, patients, parents, and family members describe active music-making as a coping mechanism for pain, discomfort, stress, anxiety, and boredom. Music-making increases the children’s and significant others’ relaxation and sleep quality and is associated with pleasure and bonding [17]. Two articles report parents’ perspectives [18] and adolescents’ perspectives [19] on music-induced mechanisms of action in relation to positive coping, resilience, social support, and family function in an RCT stemming from the research team around Sheri L. Robb (cf. [10]).*Quantitative studies*: In their RCT, Robb et al. report improvement in health outcomes of courageous coping, social integration, and family environment during high-risk cancer treatment using therapeutic music video interventions [10]. Another RCT and a single case design pilot study from Robb et al. point out the positive effects of active music interventions on multiple biomarkers to improve understanding of dose–response effects [20, 21], as well as treatment fidelity in music-based play interventions for young children with cancer and their parents [22]. In addition, a pilot RCT by Robb et al. investigated the feasibility and acceptability of parent-delivered active music engagement. This intervention was successful in providing emotional relief to children but was not well received by parents due to the unfavourably planned intervention content [23].*Qualitative studies*: The qualitative study investigates the effects of musical training on the psychological well-being and quality of life of brain tumour survivor children, their parents, and caregivers. Although positive effects were reported, the factors that stimulated the efficacy are still unknown [24].

**Table 1 Tab1:** Systematic keyword-based literature search

**No**			**Searches**	**Results**
**PubMed from 2010 to 2023; searched 12.01.2023**				
1		All fields	“music therapy” OR “music intervention” OR “music based”	13.436
2	AND	All fields	“oncology” OR “cancer”	803
3	AND	All fields	“children” OR “paediatric”	129
4	AND	All fields	“famil*” OR “parents”	52
**Cochrane from 2010 to 2023; searched 12.01.2023**				
1		All fields	“music therapy” OR “music intervention” OR “music based”	2.745
2	AND	All fields	“oncology” OR “cancer”	279
3	AND	All fields	“children” OR “paediatric”	2
4	AND	All fields	“famil*” OR “parents”	0

Though these publications strongly recommend the inclusion of significant others in the practice and research of music therapy, there is no RCT in interactive music therapy focusing on effects in the child-significant other interaction.

### Epidemiology

Although the probability of a child to fall ill with cancer in the first 18 years of life is only 0.3%, oncological and haematological diseases are the second most common cause of death in children and adolescents [25]. In Germany, about 2200 young people under the age of 18 are affected every year; the Society for Paediatric Oncology and Haematology [25] speaks of an incidence of around 170 new cases per 1 million children in this age group. The most common types of cancer in children and adolescents are leukaemia (about 30%), followed by tumours of the central nervous system (about 24%), lymphomas (about 14%), soft tissue sarcomas (5.7%), neuroblastomas (5.5%), and nephroblastomas (about 4.2%) [25].

### Clinical picture

According to a definition of the PSAPOH paediatric oncology patients are confined in an existential stress situation. They oscillate with their families in a field of tension caused by extreme experiences. Following the shock of a life-threatening diagnosis, everyday life starts to break down and is soon to be determined by hospital stays including invasive medical interventions and strict therapy plans as well as social restrictions in the home environment. In addition to physical effects, children with cancer and their relatives are confronted with emotional distress caused by worries, fears, feelings of helplessness, isolation, and the loss of control and autonomy. Within these affected social systems, mainly the family, individual and systemic coping strategies must be developed which, in conjunction with existing interaction patterns, have a great impact on how these stressful situations are dealt with [2].

### Music therapy

Although music therapy is still far from being an integrated part of multi-professional paediatric clinic teams in German-speaking countries, it is recommended as an integral part of the inpatient psychosocial care for children and adolescents with cancer [26, 27]. In addition to more linguistically oriented forms of therapy and counselling, it offers the possibility to express, experience, and reflect on an emotional-intuitive level through musical creation [2]. The identity-building act of self-experience creates a space in which the children and adolescents can confront the internal and external challenges of their current existential situation. They deal with physiological, psychological, and social conditions in musical improvisation [28]. Individual and age-specific developmental phases as well as developmental-psychological processing strategies are considered. In its professional profile of art and music therapists, the PSAPOH recommends music therapy for (1) patients with physical stress criteria, such as drastic changes in body image, severe courses of illness, painful medical interventions, recurrences, prolonged hospital stays, isolation (e.g,. in bone marrow transplants), immobility due to treatment, speech impairments, motor and sensory disabilities, and poor prognosis; (2) patients with psychological stress criteria, such as severe anxiety, processing problems (e.g,. regression, severe withdrawal, aggressive behaviour), compliance problems, and particular psychological and vegetative reactions (e.g., depressive symptoms, perceptual disorders, dissociation, decompensation); (3) patients in palliative therapy; (4) patients with existing language barriers; and (5) outpatients and follow-up care in the case of permanent changes in body image or physical disabilities, reintegration difficulties, behavioural problems occurring after the end of intensive therapy, the child’s wish to continue the accompaniment, identity problems, traumatic experiences and their processing, stigmatization, and difficulties in coping with the disease and mourning [2].

### Efficacy of music therapy

In the health technology assessment (HTA) report on music therapy published in 2019, the German Institute for Quality and Efficiency in Health Care [1] describes indications and evidence for a short-term efficacy of music therapy in relation to psychological endpoints such as fatigue, mood swings, anxiety, and health-related quality of life [1]. In the studies we evaluated and selected for this purpose, evidence was found that music-based interventions have positive effects on psychological well-being [17, 24], competence, resilience, and interactive affect regulation [14]. Positive effects have been found in relation to cognitive and physiological aspects [12], as indicated by biomarkers in form of cortisol and immune function measurements [20, 21] and measurement of heart rates, respiratory rates, and blood pressure [29]. Music therapy has also been claimed to support family functioning and social integration [10, 16, 18, 19, 30].

### Pilot study

RCTs are considered the most rigorous standard of evidence-based research. They are often complex, time-consuming, and expensive. Before implementing a confirmatory RCT, a feasibility RCT should be conducted that replicates all the essential elements of the planned larger trial [31]. This study is the first feasibility RCT, and the first RCT in general, which focuses not only on the affected children but also on their equally important significant others. INMUT is also the first feasibility RCT to use both the blind observer-based music therapy assessment of parent–child interaction (APCI) [32, 33] in paediatric oncology and a self-report questionnaires for the child as well as the significant other addressing quality of life, systemic and psychological functioning, psychosocial burden, resources, and goal attainment. The aim is to investigate the needed conditions for a subsequent confirmatory RCT which could save costs by carrying out the interventions more efficiently in the future with a well-powered study sample [34].

### Aims and objectives

The main focus of this assessor-blind, prospective, multicentric feasibility RCT is the implementation of the necessary recruitment procedures, for the inclusion of child-significant other dyads (INMUT-KB), the music therapy as usual with only the child (MUT-K), and a wait-list group (WLG). Further objectives were considering procedures for data analyses, the exploration of potential effects and the calculation of child-significant other dyads needed for a subsequent confirmatory RCT. Particularly in vulnerable patient groups such as the clientele described here, a careful estimation of the case numbers is necessary in order to be able to validate the primary and secondary effects in the confirmatory RCT, without spending resources on a unnecessarily large sample size that bears the risks of bias and noise [34, 35]. For that purpose, we will descriptively and exploratively investigate the following research questions (RQ).Feasibility and acceptability of research methodology*RQ1.1*: Is it possible to recruit and randomize enough child-significant other dyads according to the study protocol? What prevents inclusion, and what causes dropouts?*RQ1.2*: Is it possible to recruit enough music therapists with adequate qualifications at the co-operating clinics? Can supervisors be found to provide the music therapists with professional support?*RQ1.3*: Have the music therapists been successfully certified as raters of the assessment of parent–child interaction (APCI)? Is a blinded implementation of the APCI feasible in the study? Can supervisors be found to provide the APCI raters with professional support?

2.Feasibility and acceptability of the interventions*RQ2.1*: Do child-significant other dyads accept and adhere to the intervention as measured by APCI ratings (T1, T2, and T10)?*RQ2.2*: How do the APCI raters rate the implementation of the assessment (T1, T2, and T10) and their own manual adherence?*RQ2.3*: Do the child-significant other dyads accept and adhere to the music therapy interventions (T3–T9)? Can the individual conditions of the sample in the three study arms (INMUT-KB), (MUT-K), and (WLG) be met?*RQ2.4*: How do the music therapists assess the implementation of the music therapy interventions (T3–T9) and their own manual adherence?*RQ2.5*: What additional benefits and barriers (T1–T10) result from the significant other’s participation in the child’s music therapy session? How do they perceive their participation in this research study? Do they report adverse events during the study period, and if yes, which ones?

3.Estimation of effect sizes*RQ3.1*: How likely is it that potential between-group effects of the interventions by INMUT-KB compared to MUT-K are due to the involvement of the significant others in the music therapy interaction?*RQ3.2*: What is the estimated within-subjects effect size and 95% CI for change in the proposed primary outcome, the APCI score, which encompasses measures of mutual attunement, nonverbal communication, and parental emotional response from baseline to the end of music therapy?*RQ3.3*: What is the estimated within-subjects effect size and 95% CI for change in the proposed secondary outcome, i.e. subjective goal achievement, quality of life, system-related functional level, psychosocial stress, psychosomatic complaints, and resources from baseline to the end of music therapy?

## Methods

### Design

This study is planned as an assessor blind, prospective, multicentric feasibility RCT with subsequent intervention. A total of 52 clients will be randomized to either the newly developed music therapy (INMUT-KB; *n* = 21), the music therapy as usual (MUT-K; *n* = 21), or the wait-list group (WLG, *n* = 10). The intervention outcome will be measured at three assessment points: baseline; post-intervention (primary endpoint), and 3-month follow-up.

### Inclusion and exclusion criteria

#### Child-significant other dyad

The study will include *children* with (1) an oncological/haematological disease in acute inpatient treatment with chemotherapy and/or radiotherapy, (2) age range between 5 and 13 years, and (3) adequate language skills for study-related self-reporting. Exclusion criteria encompass the following: (1) a serious physical comorbidity with impairment of brain-organic functions, (2) auditory impairment, (3) BMI < 14, (4) insufficient language skills, and (5) withdrawal of informed consent for study participation. Inclusion criteria of *significant others* refer to the following: (1) their role as a significant other (e.g. mother, father, aunt, caregiver) and (2) sufficient language skills for study-related self-reporting. Exclusion results if (1) informed consent for study participation is withdrawn.

#### Therapists

Inclusion criteria for music therapists encompass a state-recognized degree from a music therapy institution certified by the German Music Therapy Association (DMtG) and professional experience in a clinical context, particularly in the fields of paediatrics and oncology/haematology. Additionally, for the rating of the child-significant other dyads in the context of the music therapy assessment, they must be certified for the APCI [32, 33].

### Recruitment

#### Patients and significant others

Recruitment will start in 2023 and end when 52 child-significant other dyads are included which is expected to be in autumn 2024. The medical management and interprofessional team of the cooperating clinics, i.e., the Community Hospital Herdecke, Clinic Center Dortmund, and Vestic Children’s Clinic Datteln, will call attention of the cancer-affected children and their significant others towards this study within the inpatient setting. Prior to that, we will have informed the medical management and the interprofessional team about the study and will have distributed flyers and study information to them. All patients will present themselves to the study team, and no patients will be referred.

#### Therapists

Recruitment started in 2021, and we already included 9 music therapists with a state-recognized degree from a music therapy institution certified by the German Music Therapy Association (DMtG). The certification process for the primary outcome, i.e. the assessment of parent–child interaction (APCI) [32, 33], began in November 2021. A 3-day training was followed by a trial phase with five non-clinical child-significant other dyads for each music therapist. The implementation of the assessments, embedding the APCI survey in the statistical programme, and the writing of the APCI reports were accompanied and reviewed individually by the APCI trainer and concluded with a joint meeting. Certification took place after completion of all supervisions by the APCI trainer in August 2022.

### Study procedures

Design, assessments and patient flow can be found in Fig. 1, assessment measures and application plan can be found in Table 2.

**Fig. 1 Fig1:**
[figure not shown]
Design, assessments and patient flow (CONSORT chart). Note: APCI Assessment of Parent-Child Interaction, DEMO Demographic Data Collection, KINDL Children and Young People Quality of Life, EXIS Experience in Social Systems, BAS Burden Assessment Scale, SCL-9k Symptom Checklist, WIRF Witten Resources Questionnaire

**Table 2 Tab2:** Assessment measures and application plan

**Purpose**	**Perspective**	**Domain**	**Instrument**	**Screening**	**Before the start of T1**	**1st & 2nd hour of therapy**	**3rd to 9th hour of therapy**	**10th hour of therapy**	**After therapy T10**	**3 months after ending of therapy T10**
					**Pre-T1**	**T1–T2**	**T3–T9**	**T10**	**Post-T10**	**Cat-T11**
Screening	MD	Clinical diagnosis, Cancer treatment	CD	X						
Demographic	P, SO, T, A	Demographic data	DEMO		X					
Primary Outcome	A	Mutual attunement	APCI			X		X		
	A	Nonverbal communication	APCI			X		X		
	A	Emotional parental response	APCI			X		X		
Secondary Outcome	P, SO	Subjective goal achievement	GAS		X				X	X
	P, SO	Quality of life	KINDL		X				X	X
	P, SO	System-related functional level	EXIS		X				X	X
	SO	Psychosocial burden	BAS		X				X	X
	SO	Psychosomatic complaints	SCL-9k		X				X	X
	SO	Resources	WIRF		X				X	X
Process	P, SO, T, A	Significant moments	SM			X	X	X		
Quality	T, A	Manual adherence	AC			X	X	X		

*P* Patient, *SO* Significant Other, *A* Assessor, *T* Therapist, *MD* Medical Doctor, *CD* Clinical Diagnosis, *APCI* Assessment of Parent-Child Interaction, *DEMO* Demographic Data, *KINDL* Children and Young People Quality of Life, *EXIS* Experience in Social Systems, *BAS* Burden Assessment Scale, *SCL-9 k* Symptom Checklist, *WIRF* Witten Resources Questionnaire, *GAS* Goal Attainment Scaling, *SM* Significant Moments, *AC* Adherence and Competence

#### Screening 

The medical management of the cooperating clinics will provide the screening of inclusion criteria. If the inclusion criteria are met, the child and significant other will receive the recruitment information. The information material and consent forms are specially designed for children; if they are not yet able to write themselves, their parents or guardians do this on their behalf. The child’s consent is a prerequisite for the realization of each session. They can refuse to participate at any time. After having obtained informed consent, the child-significant other dyad will be randomly assigned to one of the three study arms and informed about their assignment. Together with the interprofessional team of the responsible clinic, it will be decided whether the music therapy will take place on an outpatient basis, i.e. the Nordoff/Robbins Music Therapy Centre, Witten, or on an inpatient basis in the clinics, either in the music therapy unit or on the hospital wards.

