#### Baseline (pre-T1, T1/T2)

The paper–pencil baseline survey will be completed by all children (approx. 10 to 15 min) and significant others (approx. 20 to 30 min) (pre-T1), i.e. up to a maximum of 3 days prior to the APCI with its two manualized entry music therapy sessions (approx. 25 min each) (T1/T2). The APCI music therapy sessions will be video-recorded and evaluated using the APCI online programme. APCI raters are blinded and will give information about possible significant moments in T1/T2 and about their adherence to the APCI manual based on self-evaluation. The child and significant other will also provide information about their significant moments if present. Two independent student raters will rate one of the two APCI sessions for APCI manual adherence.

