### Randomization

#### Treatment allocation

We will use block randomization of 10 to 12 child-significant other dyads each. From the total of 52 child-significant other dyads to be included, 21 dyads will be randomly assigned to the INMUT-KB, 21 dyads to MUT-K, and 10 dyads to WLG. The randomization plan will be carried out by an independent research assistant at the Heidelberg University Hospital, who is not otherwise involved in the study, using the statistical software R version 4.2.1 [36, 37]. The randomized allocation of the child-significant other dyads into the three study arms will be performed after finalization of the screening. The allocation will be carried out by means of sealed envelopes (“sealed envelope method”), which will be opened in the presence of the child-significant other dyads together with a study staff member.

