### Blinding and Allegiance

#### Blinding

The APCI sessions at baseline (T1/T2) and end of therapy (T10), indicating the primary endpoint of this feasibility RCTs, will be blindly conducted by APCI raters. The music therapists will know the assignment as they will also guide the INMUT-KB and MUT-K (T3 to T9). APCI raters will not be the music therapists who are otherwise working with the child-significant other dyads. The included child-significant other dyads will be informed about their assignment and the general aims of the study, but not about specific hypotheses of any endpoint.

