#### Estimation of effect sizes

For *estimation of effect sizes*, and because child-significant other dyads treated by one music therapist (within-group) may be more like each other compared to those treated by another music therapists (within-group), a two-level linear regression analysis will be performed to account for potential clustering effects at higher levels (i.e. child-significant other dyads nested within therapists). The intraclass correlation (ICC) coefficient from the random intercept model with child-significant other dyad (Level 1) and therapist (Level 2) will be calculated for the proposed primary outcome (APCI) [59]. An ICC greater than zero will indicate a clustering effect, and any statistical analysis must be adjusted for these effects. All proposed outcomes will be analysed as intention to treat (ITT; *n* = 52) using mean scores (*M*), standard deviations (*SD*), and 95% *CI*. The ITT calculation will be regardless of whether the child-significant other dyads will violate the inclusion criteria, whether they complete the music therapy, or whether they will withdraw from the study due to protocol deviations (e.g. concurrent music therapy during the study period [60]). Missing values of less than 20% will be replaced with the conditional mean value of the subgroups (INMUT-KB, MUT-K, WLG). This will be compared to per-protocol analyses. We will use mixed-design ANOVAs (group: INMUT-KB, MUT-K, WLG; status: child-significant other dyad, child alone; time: baseline, post-intervention, 3-month follow-up), adjusting for baseline scores considering demography as well as outcome data. Because treatment outcome will be measured at three assessment points, within-group effects will be further analysed by comparisons between baseline and post-intervention (Contrast A) and by comparisons between post-intervention and 3-month follow-up (Contrast B) (RQ3.1). Effect sizes will be presented as partial eta-squared values (η^2^) and Cohen’s *d*, calculated as the difference between the means divided by the pooled standard deviation $$(d=\frac{{x}_{1}^{2}-{x}_{1}^{2}}{\sqrt{{s}_{1}^{2}+{s}_{2}^{2}}/2})$$. Classification of *effect sizes* will be as follows: η^2^ ≥ 0.010, small effect; η^2^ ≥ 0.060, medium effect; η^2^ ≥ 0.140, large effect; Cohen’s *d* 0.20, small effect; *d* ≥ 0.50, medium effect; and *d* ≥ 0.80, large effect [61] (RQ3.2, RQ3.3).

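### Dyads learn their arm before the pre-T1 questionnaires and goal setting, so the self-reported baseline can be influenced by the allocation, and some randomised dyads may have no baseline

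*Protocol article*

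**What the plan says.** Three sections of the protocol article fix when the arm is assigned and who knows it.

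- Screening: once consent is obtained, "the child-significant other dyad will be randomly assigned to one of the three study arms and informed about their assignment".
- Treatment allocation: "The randomized allocation of the child-significant other dyads into the three study arms will be performed after finalization of the screening". The arm is held in sealed envelopes, "which will be opened in the presence of the child-significant other dyads together with a study staff member".
- Blinding: "The included child-significant other dyads will be informed about their assignment and the general aims of the study". Only the specific hypotheses are withheld from families.

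The baseline is described next. Under Baseline (pre-T1, T1/T2), all children and significant others complete the paper survey "up to a maximum of 3 days prior to the APCI with its two manualized entry music therapy sessions". Table 2 marks GAS, KINDL, EXIS, BAS, SCL-9k and WIRF at pre-T1, and the APCI at T1–T2.

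Under Estimation of effect sizes, the mixed-design ANOVAs are run "adjusting for baseline scores considering demography as well as outcome data", and Contrast A compares baseline with post-intervention. RQ3.2 and RQ3.3 are worded as change from baseline to the end of music therapy.

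**The concern.** A baseline is safe for adjustment, or as the start of a change score, because randomisation cannot have affected it. Here allocation is tied to the end of screening rather than to completion of the baseline. Families answer pre-T1 knowing whether they will have joint therapy, child-only therapy or a wait.

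The measures differ in how exposed they are. KINDL asks about the last week and EXIS about the last two weeks, so a reaction to the allocation can fall inside the recall window. GAS goals are free text and can be chosen to suit a known arm. Disappointment at being put on the wait-list would act mainly on comparisons with that group.

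There is also a missing-data consequence. A dyad that leaves between the envelope and pre-T1 has been randomised, so it belongs to the ITT set, but it has no questionnaire baseline. The stated replacement rule covers missing values below 20% and does not clearly reach such a dyad.

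The analyses are exploratory, but the effect trends have a use. The abstract's Discussion and the Aims and objectives section feed them into the sample size of the confirmatory trial and the judgement of whether to run it.

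**Working it through.** **Order of events.** Consent, assignment and disclosure are explicitly linked in Screening, and Treatment allocation agrees. That pre-T1 comes later is inferred from three places that agree with each other:

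1. The Baseline section follows the Screening section.
2. Table 2 runs from screening to pre-T1 to T1–T2.
3. The RQ1.1 flow list under Measures counts inclusion (item 4), then drop-out before pre-T1 (item 5), then completion of pre-T1 (item 6). RQ1.1 also wants drop-out within each arm at all measurement times, which fits allocation before pre-T1.

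Nothing in the text places pre-T1 before the envelope.

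**Size of a possible bias.** The plan states no figure to reproduce, and it gives neither a baseline shift nor a baseline-outcome correlation. The following are assumptions: one arm's measured baseline moves by δ = 0.1 to 0.3 SD; the correlation is r = 0.3 to 0.7; a fraction k of the shift is still present at post-T10; the true effect is 0. For the shifted arm minus the other arm:

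- bias of the change-score difference = kδ − δ = (k − 1)δ
- bias of the baseline-adjusted difference = kδ − rδ = (k − r)δ

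*Shift faded by post-T10 (k = 0).* The change score is biased by −δ, that is 0.1, 0.2 or 0.3 SD in absolute size. The adjusted difference is biased by −rδ, in absolute size:

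| r | δ = 0.1 | δ = 0.2 | δ = 0.3 |
|---|---|---|---|
| 0.3 | 0.03 | 0.06 | 0.09 |
| 0.5 | 0.05 | 0.10 | 0.15 |
| 0.7 | 0.07 | 0.14 | 0.21 |

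A simulation of 400,000 dyads per cell agreed: change-score bias −0.100 to −0.305, adjusted bias −0.030 to −0.214, and the comparison of post-intervention values alone within 0.005 of zero.

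*Shift persists fully (k = 1).* The change score is biased by 0. The adjusted difference is biased by (1 − r)δ, with the opposite sign: from 0.3 × 0.1 = 0.03 to 0.7 × 0.3 = 0.21 SD.

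**Yardstick.** The plan calls d = 0.20 a small effect.

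**After the fix.** With pre-T1 completed before the envelope is opened, δ = 0 for the questionnaire baseline by design, and both expressions lose their baseline term. No sample-size figure changes.

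**The case against.** The strongest reply concerns scope and size, and much of it stands.

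- **Primary outcome and main contrast.** The confirmatory sample size rests on INMUT-KB against MUT-K, two arms that both receive music therapy; wait-list disappointment lies outside that contrast. The APCI is scored by blinded raters, so at baseline knowledge of the arm acts mainly through how the dyad behaves. The BAS looks back 6 months and should move less. All this limits the risk without removing it for recent self-reports and goals.
- **Noise.** With 21 per arm the standard error of an unadjusted standardised difference is about √(2/21) = 0.31, so a bias of 0.10 is about a third of it. True, but a bias is not shown by the confidence interval, and the point estimate may still steer the confirmatory design.
- **Every effect estimate is affected.** A reader might infer this. The documents do not support it: Contrast B runs from post-intervention to follow-up and does not start from baseline. GAS goals are classified free text, so goals written to fit the arm are a problem of interpretation rather than a shifted covariate with a bias of rδ.
- **Treatment setting.** A reader might infer that the inpatient or outpatient decision is made knowing the arm, since "it will be decided whether the music therapy will take place on an outpatient basis" follows the assignment sentence in Screening. The text gives no clear time order for that decision, and it is not a baseline measurement.
- **Opening only after T2.** This might look like the obvious remedy. Table 2 labels T1–T2 as the first two hours of therapy, and RQ1.1 sets out to measure early drop-out by arm, so requiring it would have a real cost.
- **Early drop-out is already counted.** It is, by arm, but counting it does not supply the missing baseline.

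**Conclusion.** The point holds for the order of procedures. Assignment and disclosure come straight after consent and screening, and everything shown places pre-T1 and APCI T1/T2 afterwards; the one reservation is that Fig. 1 is not available. The documents show an opportunity for bias, not its occurrence or size. Under the stated assumptions the bias is 0.1 to 0.3 SD in change scores and 0.03 to 0.21 SD in adjusted differences if the shift fades. If it persists fully, the change-score bias is nil and the adjusted bias is of similar size but reversed sign. The upper end reaches the plan's own small effect of 0.20. Exposure is greatest for recent self-reports, GAS goals and wait-list comparisons, and smaller for the APCI and BAS. Because the analyses are exploratory, what is at stake is the planning information for the confirmatory trial. The change should be made because it is cheap, not because the present estimates are known to be wrong.

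**What to change.** For all further dyads, complete the pre-T1 questionnaires and goal setting after consent and before the envelope is opened, and say so in Screening and Treatment allocation. Where logistics allow, also hold APCI T1/T2 before opening. Flag dyads enrolled under the present order and report their baseline as measured after allocation.

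The cost is small: the envelope is opened slightly later, and losses before opening are counted in the flow overall and no longer by arm. The change protects the baseline only; self-reports at post-T10 are still given by families who know their arm.
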